#### Adverse Events

An AE is defined as any untoward medical occurrence experienced by a subject, whether or not considered drug related by the investigator. For the current study, all AEs will be coded using MedDRA (version 23.1) by 4Pharma.

AEs are:

- Unfavourable changes in general condition.
- Subjective or objective signs/symptoms.
- Concomitant diseases or accidents.
- Clinically relevant adverse changes in laboratory parameters observed in a subject in the course of a clinical study.

AEs comprise all disturbances of general health status, subjective and objective disease symptoms (including significant, clinically relevant laboratory abnormalities), concomitant diseases, and accidents observed in the context of a clinical trial, irrespective of a possible causal relationship with IMP administration.

All AEs, whether volunteered, elicited, or noted on physical examination, will be recorded throughout the study, i.e., from the screening visit until the end of study participation. AEs that occur prior to the first study product administration will be reported separately from treatment-emergent adverse events, which will be of particular interest.

When an AE occurs, the first decision will be to determine its severity and relationship to the study products.

The severity of AEs will be categorized as follows:

- Mild = Experience is minor and does not cause significant discomfort to subject or change in activities of daily living (ADL) compared to subject baseline; subject is aware of symptoms but symptoms are easily tolerated.
- Moderate = Experience is an inconvenience or concern to the subject and causes interference with ADL compared to subject baseline but the subject is able to continue with ADL.
- Severe = Experience significantly interferes with ADL and the subject is incapacitated and/or unable to continue with ADL compared to subject's baseline.

The relationship of an AE to study products will be categorized as follows:

- Related; when there is a reasonable possibility of a causal relationship between study product and an AE (i.e. adverse drug reaction, ADR);
- Not related; when an AE does not follow a reasonable temporal sequence from product administration or when an AE can be reasonably explained by other factors including underlying disease, concomitant drugs or concurrent treatment;
- Study treatment not initiated.

The investigator marks on the AE-SD form all AEs, indicating his/her assessment of a causal relationship to study treatments using the categories above.

As far as possible, each AE will also be described by its duration (start and end date and time), and the action(s) taken, and, as relevant, the outcome.

#### Serious Adverse Events

A Serious Adverse Event (SAE) is any adverse event occurring during the study that results in any of the following outcomes:

- Death.
- A life-threatening AE that placed the subject, in the view of the investigator, at immediate risk of death.
- Inpatient hospitalization or prolongation of existing hospitalization.
- A persistent or significant disability/incapacity.
- A congenital anomaly/birth defect.
- Important medical event that may require medical or surgical intervention to prevent one of the above outcomes.

An important medical event that may not result in death, be life-threatening, or require hospitalization may be considered an SAE when, based upon appropriate medical judgment, it may jeopardize the subject and may require medical or surgical intervention to prevent one of the outcomes listed in this definition.

In case of an SAE, the investigator will contact the Sponsor's designated Medical Lead as soon as possible. SAEs must be reported within 24 hours of becoming aware of an SAE, regardless of the time that may have elapsed since the time the event occurred and regardless of the causal relationship of IMP to the event. An initial SAE report will be submitted to the Sponsor (and Fimea) as agreed between the parties, and a follow-up report will be provided later, if indicated. Follow-up reports to an SAE should be prepared if any relevant change in the condition of the study subject occurs after the initial report. SAEs should be followed up until resolved or until the event is considered chronic and/or stable outcome.

The contact person and address of the Sponsor for SAEs are:

, MD, Porin perusturvayhtymä  
e-mail [[name]](mailto:[name])  
tel. [name]

#### Suspected Unexpected Serious Adverse Reactions

An unexpected adverse drug reaction is any ADR, the specificity or severity of which is not consistent with the summary of product characteristics of HCQ. Suspected unexpected serious ADRs (SUSARs) are subject to expedited reporting to Fimea. The investigator reports all authority-reportable AEs to the Sponsor and to Fimea, as agreed between the parties.

#### 7.4 Assessments of pharmacokinetics, pharmacogenetics and immunogenetics

Blood samples will be collected at the 2- and 4-week visits in order to monitor treatment compliance by concentration analysis of HCQ. The HCQ concentration results will additionally be used to perform population pharmacokinetic modeling in order to evaluate associations between drug exposure and relevant patient outcomes.

A separate whole-blood sample (with EDTA as anticoagulant) will be collected from consenting participants for later DNA extraction and pharmacogenetic (PG) analysis of genetic variation in drug metabolizing enzymes and exploration of immunogenetic associations in the study outcomes. The PG samples will be tested with the Abomics PGx test platform that includes the genes for ALDH2, BCHE, CYP1A2, CYP2B6, CYP2C19, CYP2C9, CYP2D6, CYP3A5, DPYD, F2, F5, G6PD, IFNL3, SLCO1B1, TPMT, UGT1A1 and VKORC1, of which at least CYP2D6 is known to be involved in the metabolism of HCQ. The PG results will be used for interpretation of the HCQ-related outcomes of the study. Immunogenetic analysis is carried out for HLA haplotypes, but it may be expanded to other genes related to immune functions and susceptibility to Covid-19 infection and its manifestations. The blood sample for DNA extraction may be collected at any time during the study. The PG analysis and the immunogenetic analysis are exploratory and optional, and will only be carried out if sufficient numbers of samples become available for meaningful analysis.

### 8 STATISTICS AND DATA MANAGEMENT

#### 8.1 Estimation of sample size

Up to 600 subjects will be included in the study. The number of hospitalizations due to Covid-19 infection within four weeks of entry into the study is a main outcome measure of the current study. Assuming a hospitalization rate of 15 % in the study population, and a 50 % reduction in the risk for hospitalization in the group treated with HCQ, a treatment group size of 278 provides 80 % power to detect a statistically significant treatment effect at  $p < 0.05$ . Since the other efficacy-related evaluations are of secondary/explorative nature in this study, no formal sample size calculations have been performed for these endpoints. For a hospitalization risk of 10 %, the group size required for 80 % power would be 435, and for a risk of only 5 %, 906 subjects per group would be required for 80 % power. As the true risk of hospitalization in the study population is unknown, and as an effect size of less than 50 % may also be considered clinically significant, both expansion of the trial beyond the initial catchment region of Satakunta and meta-analysis by combining the study results with those derived from other similar patient populations is intended.

Detailed information on the power calculations will be provided in a separate Statistical Analysis Plan (SAP). The power calculations were made using nQuery Advanced version 8.5.

#### 8.2 Statistical methods

A summary of the statistical methods is given below.

### 8.2.1 Statistical Analysis Plan

Detailed statistical analysis information will be provided in the SAP before database lock.

### 8.2.2 Statistical hypotheses

The number of hospitalizations due to Covid-19 infection within four weeks of entry into the study is the primary outcome measure of the study. The following null hypothesis will be tested corresponding to this endpoint:

$H_0$ : there is no difference in the number of hospitalizations due to Covid-19 infection within four weeks of entry into the study between the HCQ and placebo groups.

The null hypothesis will be tested against the following alternative hypothesis:

$H_1$ : treatment with HCQ will reduce the risk of hospitalization because of Covid-19 infection within four weeks of entry into the study.

The evaluations for secondary and exploratory endpoints will mainly be based on descriptive statistics.

### 8.2.3 Data sets to be analyzed

A subject classification document including a list of protocol deviations with a clinical classification of the deviations and the definition of the analysis datasets will be prepared and approved after database lock before opening of the randomization code.

Three main analysis data sets will be constructed. The intention-to-treat (ITT) data set will include all enrolled subjects. The safety data set will consist of all subjects having received at least one dose of study medication. The per-protocol (PP) dataset including all subjects with SARS-CoV-2 PCR-confirmed Covid-19 infection who received at least four days of treatment with study medication and for whom evaluable outcome data are available.

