## 2.4 Primary endpoint

The primary endpoint of the study is:

- number of hospitalizations due to Covid-19 infection within four weeks of entry into the study; the study hypothesis is that treatment with HCQ will reduce the risk of hospitalization because of Covid-19 infection, and the sample size estimate of the study is based on the need to test this hypothesis.

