## 3.2 Randomization and blinding

This is a double-blind study. The participants and study personnel will remain blinded to the treatment allocation by having both investigational medicinal products (IMPs) packed in identical containers. Masking of the treatments is performed by re-

formulation of the IMPs so that the HCQ capsules and the placebo capsules have identical appearance.

At the screening visit, subjects who have signed the informed consent form (ICF) will be given screening numbers beginning from S1001. Randomization will be performed when the investigator has confirmed a subject's eligibility. After randomization, subjects will receive subject numbers starting from 1001 and will be allocated to the treatment assigned to each subject number as indicated by the randomization scheme. Detailed information on randomization will be provided in a separate Randomization Plan/Request document prepared by the DM provider.

In case of a medical emergency, the treatment code may be opened in the electronic data management system of the study (Viedoc™). Unblinding by the investigator is restricted to situations when knowledge of the treatment allocation is considered necessary for the safety and medical treatment of the subject. The reason for unblinding will be documented, along with the date and time of unblinding and an identifier of the person who broke the code. In case of a subject's death or hospitalization, that subject's participation in the study is concluded, and the treatment code of that subject will be opened by the Medical Lead of the study. For hospitalized subjects, this information will be communicated to the hospital in charge of the patient's subsequent medical care. De-identified unblinded information on deaths and hospitalizations will also be provided to the SC for ongoing evaluation of the participants' safety.

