#### 4.7 Withdrawal of subjects

A subject has the right to withdraw his/her consent without any need to justify this decision. However, efforts should be made to find out the reason of the withdrawal. Possible withdrawal will not have any negative effect on the subject's future medical care.

The investigator may withdraw a subject from the study at any time based on the investigator's clinical judgement. A subject will be withdrawn from further IMP dosing if he or she starts a prohibited medication, develops suspected severe or moderately severe pneumonia, requires treatment in hospital, or other inclusion and exclusion criteria are no longer met. A subject will also be withdrawn from further IMP administration if she/he fails to comply with the trial protocol, or an AE jeopardizing her/his well-being occurs, or if the discontinuation is otherwise in the best interest of the subject.

Subjects who discontinue the study drug prematurely will be encouraged to attend all study visits and complete all study assessments. Still, subjects will retain the right to withdraw their consent for the study, and no study procedures should be carried out against their will.

All information collected from a withdrawn subject, including the reason of withdrawal, will be included in the study file for use as study data and for purposes of verification.

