## 5.5 Procedures for monitoring of subject compliance

Treatment compliance will be evaluated by asking the participants to register any deviations from the planned treatment regimen in a participant diary to be collected at the 2-week visit and by performing concentration analysis of HCQ in blood samples collected at the 2- and 4-week visits.

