## 6.2 Treatment period

The treatment period will last 4 weeks and the actual treatment 7 days. During the treatment period, the subjects will receive HCQ or placebo capsules twice daily with meals during 7 days. In addition, all subjects will receive standard care for their Covid-19 infection, according to local treatment practice. This includes daily telephone contacts with patients who have symptoms. The script of the daily telephone interviews includes questions on possible suicidal ideation and impairment of mental health. Should the answers to these questions reveal significant adverse changes from baseline or an elevated risk for self-harm, the investigator will be informed, and will then take the necessary actions to provide appropriate psychiatric evaluation and care for the subject, without delay. The subjects will be provided with finger-tip pulse oximetry devices and with instructions on their use during the first 14 days of the treatment period.

On Day 8, all subjects will be contacted by telephone for an interview on symptoms, concomitant medications and possible AEs.

Approximately 2 weeks and 4 weeks after start of drug intake, the subjects will visit their study site for assessments. Safety laboratory tests will be taken at these visits, as well as nasopharyngeal swab samples for SARS-CoV-2 PCR analysis and blood samples for analysis of SARS-CoV-2 antibody titres, other Covid-19-related biomarkers and HCQ concentration analysis. The GAD-7 questionnaire will be completed by the subjects. In addition, they will be asked about symptoms, concomitant medications and possible AEs that might have occurred since the last contact. At the 2-week visit, body temperature and SpO2 will also be measured, and the participant diaries will be collected.

Because of the slow elimination of HCQ, the treatment period of this study is defined as starting from the first IMP intake and ending at the 4-week visit.

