### 8.2.6 Analysis of efficacy variables

For the primary variable of the study, the proportion of hospitalizations will be estimated within each treatment group. The main analysis will be made using a logistic regression model. The methods of analysis of all efficacy variables will be

provided in the SAP. At least, analysis of all primary and secondary efficacy variables will be performed for both the PP and ITT datasets.

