### 13 CRITERIA FOR PREMATURE STUDY TERMINATION

The study may be discontinued at the discretion of the Principal Investigator or the Sponsor based e.g. on the occurrence of the following:

- ADRs unknown to date in respect to their nature, severity, and duration or the unexpected incidence of known ADRs;
- New information becomes available that mandates study discontinuation, e.g. for futility or for proof of efficacy of HCQ or another type of treatment of Covid-19 infection in the patient population of this study.
- Other medical or ethical reasons affecting the continued performance of the study.
- Difficulties in the recruitment of subjects.
- Significant deviations from the study protocol.

The investigator will inform the EC and the Sponsor will inform the CA if the study is terminated prematurely. The Sponsor reserves the right to prematurely terminate the study for valid scientific or administrative reasons. The investigator will proceed to appropriate actions concerning the study subjects in the case of premature termination of the study.

A study site may withdraw from further subject recruitment at any time if sufficient resources can no longer be allocated to proper execution of the study procedures. Already enrolled subjects should be treated and followed up according to the study protocol even if a site is withdrawn from further enrollment activities.

Individual study subjects are free to withdraw from further study treatment and from further study procedures if they wish. In addition, subjects should be withdrawn by the investigator from further study medication in case the patient must be hospitalized for any reason, if the subject starts a prohibited medication or if an AE severe enough to justify discontinuation of treatment with HCQ develops. The investigator may withdraw a subject from the study at any time based on the investigator's clinical judgement. A subject will also be withdrawn from further IMP administration if she/he fails to comply with the trial protocol, or if the discontinuation is otherwise in the best interest of the subject.

Subjects who discontinue the study medication prematurely will be encouraged to attend all study visits and complete all study assessments.

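### The four-day dosing rule for the per-protocol set removes subjects because they had an early primary event, since admission itself stops dosing

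*Protocol*

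**What the plan says.** Section 8.2.3 defines the PP set as PCR-confirmed cases "who received at least four days of treatment with study medication and for whom evaluable outcome data are available". The Synopsis gives the same four-day rule twice, under Objectives and endpoints and under Statistical methods. None of the three places makes an exception for subjects whose dosing stopped because of the endpoint.

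Two sections take subjects off study medication for reasons tied to the endpoint. Section 4.7 does so if the subject "develops suspected severe or moderately severe pneumonia, requires treatment in hospital". Section 13 says that "subjects should be withdrawn by the investigator from further study medication in case the patient must be hospitalized for any reason". The primary endpoint (Section 2.4) is Covid-19 hospitalization in the four weeks after entry. Dosing occupies only the first part of that window: "The treatment period will last 4 weeks and the actual treatment 7 days" (Section 6.2).

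On use of the sets, Section 8.2.6 states: "At least, analysis of all primary and secondary efficacy variables will be performed for both the PP and ITT datasets". The ITT set keeps every subject (all randomized in the Synopsis, all enrolled in Section 8.2.3).

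**The concern.** A PP set should exclude subjects for non-adherence. Here a subject who takes every capsule as instructed and is admitted on day 2 or 3 also fails the four-day rule. The failure follows from the trial's own dosing stop, which is triggered by the primary outcome. PP thus analyses only those who reached four days of dosing without being admitted or stopped for pneumonia. Early events are lost from the numerator and the denominator alike.

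At the least, the PP analysis has fewer events than it should. If the drug changes when admissions happen, in either direction, the two arms of PP are no longer comparable and the PP estimate can exaggerate, hide or reverse the effect. An early excess of admissions on the drug is the kind of signal that PP would mostly remove.

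**Working it through.** **Inputs from the protocol.** Placebo risk 15%, a 50% reduction (so 7.5% on HCQ), 80% power and 278 per group (Section 8.1); two-sided 0.05 (Synopsis, Sample size considerations); about 600 subjects (Section 4.2), half on HCQ (Section 10), hence 300 per arm.

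**Assumed, because the protocol is silent.** The risk *e* of a primary event before four days of dosing are completed, in each arm.

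**Step 1: reproduce the plan's figure.** For two proportions with pooled variance under the null and p̄ = 0.1125:

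n = [1.960·√(2·0.1125·0.8875) + 0.842·√(0.15·0.85 + 0.075·0.925)]² / 0.075² = (0.8758 + 0.3734)² / 0.005625 = 277.5, so 278.

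This matches. The same formula gives 435 and 906 for the 10% and 5% risks, also as stated. At 300 per arm, power is 83.0%.

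**Step 2: risk in PP.** With total risk p and early risk e, PP keeps a fraction 1 − e of the arm, of whom p − e have events:

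PP risk = (p − e)/(1 − e); PP odds = (p − e)/(1 − p).

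**Step 3: equal early share f in both arms (e = f·p), planned effect.** PP odds become p(1 − f)/(1 − p). The factor 1 − f cancels in the ratio, so the odds ratio stays at (0.075/0.925)/(0.15/0.85) = 0.459. What is lost is events, out of 45 expected on placebo and 22.5 on HCQ.

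| f | Events dropped (placebo, HCQ) | PP risks | PP odds ratio | Power, formula | Power, simulation |
|---|---|---|---|---|---|
| 0 | 0, 0 | 15.0% vs 7.5% | 0.459 | 83% | 84% |
| 20% | 9, 4.5 | 12.4% vs 6.1% | 0.459 | 75% | 76% |
| one third | 15, 7.5 | 10.5% vs 5.1% | 0.459 | 68% | 69% |
| 50% | 22.5, 11.25 | 8.1% vs 3.9% | 0.459 | 56% | 57% |

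For f = 20%, the arms shrink to 291 and 295.5. The difference is 0.0628, the null standard error 0.0239 and the alternative standard error 0.0238. Power = Φ[(0.0628 − 1.960·0.0239)/0.0238] = Φ(0.67) = 0.75.

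**Step 4: equal total risk (15% in both arms), different early risk, 300 randomized per arm.** With p equal, the PP odds ratio reduces to the ratio of late risks, (0.15 − e on HCQ)/(0.15 − e on placebo).

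| Early risk, placebo vs HCQ | PP risks | PP odds ratio | Two-sided rejection |
|---|---|---|---|
| 5% vs 5% | 10.5% vs 10.5% | 0.10/0.10 = 1.00 | 5% |
| 5% vs 7% | 10.5% vs 8.6% | 0.08/0.10 = 0.80 | 12% |
| 5% vs 8% | 10.5% vs 7.6% | 0.07/0.10 = 0.70 | 22% |
| 5% vs 10% | 10.5% vs 5.6% | 0.05/0.10 = 0.50 | 58% |

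The last figure is 59% if PP itself holds 280 per arm. Exchanging the arms inverts the odds ratios to 1.25, 1.43 and 2.00, which is apparent harm.

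**Step 5: early harm.** Suppose HCQ adds 5 points of early risk and nothing later: 15% (5% early) against 20% (10% early). ITT has an odds ratio of (0.20/0.80)/(0.15/0.85) = 1.42. PP shows 0.10/0.95 = 10.5% against 0.10/0.90 = 11.1%, an odds ratio of (0.10/0.80)/(0.10/0.85) = 1.06.

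**The case against.** The strongest reply is that this touches a secondary analysis set. ITT keeps every early event, it is listed first wherever the sets are defined, and nothing in the protocol makes PP decisive. Ranking the sets is commonly left to the statistical analysis plan, which is not at hand, so the absence of a ranking is not a fault in itself. Section 8.2.3 also promises a classification document that will define the analysis sets before the randomization code is opened, and event-driven stops could be settled there. Early harm would still be visible in ITT, in the safety set and in the Steering Committee's unblinded follow-up of admissions and deaths.

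All of that stands, and it limits the severity. It does not remove the point, because the four-day rule is stated three times without exception. Deferral to the classification document is also weaker protection than it looks: Section 3.2 opens the code of each hospitalized subject during the study, so the arms of the very subjects in question are already known to some when membership is settled.

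Two stronger readings are tempting. A reader might infer that PP would show a benefit even if the drug did nothing. It would not: with an inert drug under blinding, the early shares are equal in expectation, the odds ratio is 1.00 and rejection is 5%. The 0.50 case needs a drug that doubles early and halves late admissions, which is a large effect on timing and not the absence of one. A reader might also object that dosing cannot be verified because it rests on a "participant diary to be collected at the 2-week visit". That is a separate matter. Section 5.5 has a second source in HCQ blood concentrations, although these say nothing about placebo subjects.

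**Conclusion.** The PP definition is wrong as written and should be fixed. Read together, Sections 8.2.3, 4.7 and 13 exclude subjects because of the primary outcome, and Section 8.2.6 then analyses that outcome in the set so formed. The ITT analysis and the planned sample size are not affected.

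The certain consequence, if any events fall early, is a loss of events and power in PP; at early shares of 20% to 50% the loss is about 8 to 27 percentage points. Bias in the odds ratio arises only if the early share differs between arms, and its direction is open. Shifts of 2 to 3 points in early risk give odds ratios of 0.80 to 0.70 with rejection of 12% to 22%; the 5-point shift is an extreme case. All of these figures rest on assumed timing of admissions, since the protocol gives none.

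**What to change.** Reword the PP definition in Section 8.2.3 and at both places in the Synopsis. A subject counts as adherent if study medication was taken as planned until the earliest of day 4, hospitalization, death, or a stop that the protocol requires for worsening Covid-19. Such subjects stay in PP, and their admissions count as events. The wording should also cover subjects admitted between randomization and delivery of the medication. Those admissions cannot depend on a blinded treatment not yet taken, so either choice is defensible if it is stated.

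State in Section 8.2.6 that ITT, meaning all randomized subjects, is the primary analysis and PP is supportive. Make the change before the classification of subjects begins, so that it cannot be driven by data.

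The cost is wording. No clinical stopping rule changes. The PP set becomes a little less strict on exposure, and its estimate may be less favourable to HCQ.
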